## Abstract

**Introduction:**

Multiple myeloma is a bone marrow cancer, which predominantly affects older people. The incidence is increasing in an ageing population.

Over the last 10 years, patient outcomes have improved. However, this is less apparent in older, less fit patients, who are ineligible for stem cell transplant. Research is required in this patient group, taking into account frailty and aiming to improve: treatment tolerability, clinical outcomes and quality of life.

**Methods and analysis:**

Frailty-adjusted therapy in Transplant Non-Eligible patients with newly diagnosed Multiple Myeloma is a national, phase III, multicentre, randomised controlled trial comparing standard (reactive) and frailty-adjusted (adaptive) induction therapy delivery with ixazomib, lenalidomide and dexamethasone (IRD), and to compare maintenance lenalidomide to lenalidomide+ixazomib, in patients with newly diagnosed multiple myeloma not suitable for stem cell transplant. Overall, 740 participants will be registered into the trial to allow 720 and 478 to be randomised at induction and maintenance, respectively.

All participants will receive IRD induction with the dosing strategy randomised (1:1) at trial entry. Patients randomised to the standard, reactive arm will commence at the full dose followed by toxicity dependent reactive modifications. Patients randomised to the adaptive arm will commence at a dose level determined by their International Myeloma Working Group frailty score. Following 12 cycles of induction treatment, participants alive and progression free will undergo a second (double-blind) randomisation on a 1:1 basis to maintenance treatment with lenalidomide+placebo versus lenalidomide+ixazomib until disease progression or intolerance.

**Ethics and dissemination:**

Ethical approval has been obtained from the North East—Tyne & Wear South Research Ethics Committee (19/NE/0125) and capacity and capability confirmed by local research and development departments for each participating centre prior to opening to recruitment. Participants are required to provide written informed consent prior to trial registration. Trial results will be disseminated by conference presentations and peer-reviewed publications.

**Trial registration number:**

ISRCTN17973108, NCT03720041.

Strengths and limitations of this studyFrailty-adjusted therapy in Transplant Non-Eligible patients with newly diagnosed Multiple Myeloma (FiTNEss) will provide the first prospective data investigating the use of the International Myeloma Working Group frailty score to define appropriate dose delivery strategies for older patients.FiTNEss will explore the impact of dual-agent maintenance compared with the single-agent standard of care using a gold standard placebo-controlled design.The trial has the potential to meet a high unmet need in older patients with myeloma for whom the impact of recent therapeutic have been less marked.Wide inclusion criteria have been designed to maximise the recruitment of older, more frail patients who may not previously have been included in clinical trials.Owing to the nature of assessments and dose adaptations, blinding in the induction phase of the trial is infeasible.

## Introduction

### Multiple myeloma

Multiple myeloma is the second most common haematological malignancy with over 5500 patients diagnosed in the UK each year.^1^ Myeloma is predominantly a disease of older people, with two-thirds of patients aged over 70 years at diagnosis. The incidence is increasing as the population ages.

Over the last 10 years, the development of proteasome inhibitors (PI), immunomodulatory drugs (IMiD agents) and improved supportive care, have ameliorated outcomes for patients with myeloma such that the median overall survival (OS) is now more than 6 years for younger, fitter patients (figure 1A).^2^ However, the impact of these therapies has been less marked in the older or less fit population, particularly those over 75 years of age and/or ineligible for stem cell transplant (figure 1B). While outcomes in younger patients are largely driven by molecular risk factors present in the myeloma cell clone, there is no evidence that older patients with myeloma have more biologically high-risk disease.^3^ Differences in outcomes are likely to be accounted for by changes in patient physiology and/or increased treatment-related toxicity. Data from our previous trial Myeloma XI (ISRCTN49407852) show that as age increases, the number of participants ceasing treatment due to choice or toxicity increases (figure 2). This group therefore has a high unmet need for new, less toxic treatments and improved treatment delivery approaches.

**Figure 1 F1:**
[figure not shown]
Overall survival in MRC-IX and NCRI-XI TE pathway (A). Overall survival in MRC-IX and NCRI-XI TNE pathway (B). MRC-IX, Medical Research Council Myeloma IX trial (ISRCTN49407852); NCRI-XI, National Cancer Research Institute Myeloma XI Trial (ISRCTN68454111); TE, transplant eligible; TNE, transplant non-eligible.

**Figure 2 F2:**
[figure not shown]
Reasons for ceasing induction treatment in NCRI-XI (n=928). NCRI-XI, National Cancer Research Institute Myeloma XI Trial (ISRCTN68454111).

### Existing evidence: induction therapy

#### Treatment

Lenalidomide is an immunomodulatory agent and thalidomide derivative available as an oral preparation, which is more potent in vitro and with a different adverse effect profile than thalidomide. For example, a major benefit of lenalidomide is the absence of associated neurotoxicity or sedation seen with thalidomide, making it more tolerable; however, there is a significant rate of myelosuppression (20%), which is not seen with thalidomide. Lenalidomide is licensed, in combination with dexamethasone, for use in newly diagnosed patients with multiple myeloma who are not eligible for transplant (TNE).

With the caveats of cross-trial comparison, our recent analysis of the Myeloma XI trial suggests that the combination cyclophosphamide, lenalidomide and attenuated dexamethasone (CRDa) is not superior to Rd-continuous used in the FIRST study (Study to Determine Efficacy and Safety of Lenalidomide Plus Low-dose Dexamethasone Versus Melphalan, Prednisone, Thalidomide in Patients With Previously Untreated Multiple Myeloma, NCT00689936) in terms of progression-free survival (PFS). In addition, Myeloma XI also showed that patients in the non-intensive pathway with only a minimal or partial response to induction therapy who were randomised to receive cyclophosphamide, bortezomib and dexamethasone consolidation had better outcomes than those who did not (an increase in median PFS of 11 months (HR: 0.73; p=0.061)).^4^ However, a significant proportion of patients (394/610; 64.6%) did not make it to this randomisation due to participant withdrawal (211; 53.6% of 394), death (96; 24.4%), progression (45; 11.4%) and other reasons (42; 10.7%). These data suggest that combining IMiD agents and PI upfront may improve outcomes further, avoiding the early loss of patients and leading to improved responses, as we have seen with the carfilzomib, cyclophosphamide, lenalidomide and dexamethasone arm in the transplant-eligible pathway of the Myeloma XI study.^5 6^

Ixazomib (MLN9708) is an orally bioavailable, small molecule inhibitor of the 20S proteasome, and has shown single-agent activity in phase I/II studies alongside combination therapy with dexamethasone and more recently IMiD agents and alkylating agents.^7–9^ The oral formulation provides convenience for patients, and the slower pharmacokinetic profile reduces the neurotoxicity seen with bortezomib, suggesting the use of this new PI in combination regimens might be better tolerated.^10^ In the front-line setting, the combination of ixazomib with lenalidomide and dexamethasone (IRD) has been reported in phase I/II studies, demonstrating high response rates and good tolerability.^11^

With a favourable toxicity profile compared with either carfilzomib or bortezomib, and the benefits of oral dosing, the IRD combination represents a tolerable regimen to achieve the same combination of IMiD agents and PI in TNE patients. The Tourmaline MM-1 study demonstrated excellent efficacy and tolerability of IRD in the relapsed setting in TNE patients, supporting this hypothesis.^12^ The Tourmaline MM-02 study, a randomised, double-blind, placebo-controlled study evaluating IRd versus placebo Rd has recently been reported^13^ and showed a clinically meaningful but non-significant 13.5 month improvement in PFS in the IRd group (35.3 vs 21.8 months; HR 0.83; p=0.073). This trial used reactive dosing strategies.

#### Treatment delivery

The International Myeloma Working Group (IMWG) proposed a scoring system for patient with myeloma frailty that predicts survival, adverse events (AEs) and treatment tolerability,^14^ which can help to account for the considerable heterogeneity in outcome for TNE patients. This score combines age and the outcomes of three patient assessment tools; the Katz Activity of Daily Living,^15^ Lawton’s Instrumental Activity of Daily Living^16^ and the Charlson Comorbidity Index^17 18^ to categorise patients into three groups: fit, unfit and frail. The IMWG frailty score was subsequently shown to be predictive of both PFS and toxicity. An increase in frailty score was associated with an increased risk of death, progression, non-haematological AEs and treatment discontinuation that was independent of classical definitions of risk, including ISS stage and cytogenetic risk, and also independent of treatment regimen. As such, it was suggested to be useful in determining the feasibility of treatment regimens and appropriate dose reductions, but this remains to be prospectively validated.

### Existing evidence: maintenance therapy

Four published studies have demonstrated an important clinical benefit for the use of maintenance lenalidomide in newly diagnosed multiple myeloma in patients of all ages. Data from our previous study Myeloma XI contributes to this evidence base and in TNE patients, lenalidomide maintenance demonstrated a significant improvement in PFS compared with observation, of 24 months versus 11 months from maintenance randomisation.^19^ This improvement was seen across all subgroups of patients with multiple myeloma, including all cytogenetic risk groups and at all ages. OS data demonstrated a benefit for lenalidomide once the effect of subsequent therapies have been taken into account.^20^

Overall, the data for maintenance lenalidomide until disease progression in patients not eligible for stem cell transplant suggest that there is a clear and significant improvement in PFS and a possible OS benefit. The crucial question to answer, going forward, is whether the results seen with lenalidomide as a single agent for maintenance can be enhanced further by the use of a combination regimen.

The use of ixazomib monotherapy in the maintenance setting demonstrated efficacy and tolerability in previously untreated patients^21^ and this has recently been confirmed in the phase III Tourmaline-MM4 trial in the non-transplant-eligible setting.^22^ Adding ixazomib to lenalidomide maintenance has not been studied in a randomised phase III study.

### Existing evidence: summary

The recently developed, less toxic PI ixazomib^11^ with novel IMiD agents/PI combinations for induction and maintenance treatment needs to be evaluated in the context of the IMWG frailty score where frailty-adjusted dosing was recommended,^14^ but emphasised the need for prospective validation of their approach.

### Aims and objectives

The Frailty-adjusted therapy in Transplant Non-Eligible patients with newly diagnosed Multiple Myeloma (FiTNEss) trial aims to improve outcomes for TNE patients by investigating whether using prospective dose adjustments dependent on patient frailty will improve patients’ ability to remain on therapy, reduce toxicity, and improve outcomes from randomisation 1 (R1). The trial also aims, from randomisation 2 (R2), to investigate whether doublet maintenance therapy improve outcomes compared with single-agent lenalidomide without prohibitive toxicity.

### Trial design

The FiTNEss trial is a phase III, multicentre, randomised, parallel group trial in newly diagnosed patients with MM, who are assessed to be TNE by their treating clinician. Following R2, the trial is also double-blind placebo-controlled with the participant and treating clinician blind to treatment allocation. The following report details the trial protocol and follows the structure of the SPIRIT statement.^23^ The SPIRIT checklist^24^ can be found within the online supplemental material.

10.1136/bmjopen-2021-056147.supp1Supplementary data

## Methods

### Setting

The trial will be conducted at 87 centres around the UK (see online supplemental material), as identified via a feasibility assessment to determine the most appropriate to participate in the trial. The majority of potential participants will be identified by the research team at the time they are referred to the haematology outpatient department with suspected multiple myeloma. A smaller number of participants may be identified during inpatient admissions. Invitation to participate in the trial and provision of information will be made either during their first consultation, when routine diagnostic tests will be performed and potential treatment options discussed, or at the time they receive their diagnostic test results.

### Eligibility criteria

Adults (18 years and older) with newly diagnosed MM, by IMWG 2014 diagnostic criteria,^25^ who are TNE and who are capable of giving written informed consent will be assessed for eligibility. Eligibility will be confirmed prior to each randomisation by the principal investigator or authorised delegate and will be recorded in the participant’s medical records and on the relevant case report form (CRF). The participant will be registered into the trial prior to undergoing procedures that are specifically for the purposes of the trial and are above National Health Service standard of care.

To be eligible for R1, participants must meet all the inclusion criteria and none of the exclusion criteria outlined in box 1. Following 12 cycles of induction therapy, participants who achieve at least a minimal response (MR), according to IMWG uniform response criteria, and fulfil all the inclusion criteria and none of the exclusion criteria outlined in box 2, will proceed to R2.

Box 1Randomisation 1: inclusion and exclusion criteriaInclusion criteria:Newly diagnosed as having MM according to the updated International Myeloma Working Group diagnostic criteria 2014 requiring treatment.Not eligible for stem cell transplant.Aged at least 18 years.Meet all of the following blood criteria within 14 days before R1:Haematological:Absolute neutrophil count (ANC)≥1×10^9^/L. Unless the participant has a known/suspected diagnosis of familial or racial neutropenia in which case an ANC≥0.75×10^9^/L is allowed. The use of growth factor support is permitted.Platelet count≥50×10^9^/L, or, in the case of heavy bone marrow infiltration (≥50%) which in the opinion of the investigator is the cause of the thrombocytopenia and provided appropriate supportive measures and patient monitoring are in place, platelet count≥30×10^9^/L is permitted. Please note: Platelet transfusions are not allowed ≤3 days prior to randomisation in order to meet these values.Haemoglobin≥80 g/L. The use of red blood cell transfusions is permitted.Biochemical:Total bilirubin≤3× upper limit of normal (ULN).Alanine aminotransferase and/or aspartate aminotransferase ≥ 3 x ULN.Meet the pregnancy prevention requirements:Female participants who:Are not of childbearing potential, ORIf they are of childbearing potential, agree to practice two effective methods of contraception, at the same time, from the time of signing the informed consent form until 90 days after the last dose of study drug, ORAgree to practice true abstinence when this is in line with the preferred and usual lifestyle of the subject. (Periodic abstinence (eg, calendar, ovulation, symptothermal, postovulation methods) and withdrawal are not acceptable methods of contraception).Male participants, even if surgically sterilised (ie, status post vasectomy), must agree to one of the following:Agree to practice effective barrier contraception during the entire study treatment period and through 90 days after the last dose of study drug, ORAgree to practice true abstinence when this is in line with the preferred and usual lifestyle of the subject. (Periodic abstinence (eg, calendar, ovulation, symptothermal, postovulation methods) and withdrawal are not acceptable methods of contraception).Contraception for female and male participants must be in accordance with (and participants must consent to) the Celgene-approved Pregnancy Prevention Programme.If female and of childbearing potential, they must have a negative pregnancy test performed by a healthcare professional in accordance with the Celgene Pregnancy Prevention Programme.Able to provide written informed consent.Exclusion criteria:Smouldering MM, monoclonal gammopathy of unknown significance (MGUS), solitary plasmacytoma of bone or extramedullary plasmacytoma (without evidence of MM).Received previous treatment for MM, with the exception of local radiotherapy to relieve bone pain or spinal cord compression, prior bisphosphonate treatment, or corticosteroids as long as the total dose does not exceed the equivalent of 160 mg dexamethasone.Known resistance, intolerance or sensitivity to any component of the planned therapies.Prior or concurrent invasive malignancies except the following:Adequately treated basal cell or squamous cell skin cancer.Incidental finding of low grade (Gleason 3+3 or less) prostate cancer requiring no intervention.Adequately treated carcinoma in situ of the breast or cervix no longer requiring medical or surgical intervention.Any cancer from which the subject has been disease free for at least 3 years.Pregnant, lactating or breastfeeding female participants.Major surgery within 14 days before randomisation. This would include surgical intervention for relief of cord compression but does not include vertebroplasty or kyphoplasty.Systemic treatment, within 14 days before the first dose of ixazomib with strong CYP3A inducers (eg, rifampicin, rifabutin, carbamazepine, phenytoin, phenobarbital), or use of St. John’s wort.Any concomitant drug therapy which, in the opinion of the investigator, may lead to an unacceptable interaction with any of the agents ixazomib, lenalidomide, dexamethasone, and that cannot be safely stopped prior to trial entry. Full details of interactions can be found in the Summary of Product Characteristics.Known gastrointestinal (GI) disease or GI procedure that could interfere with the oral absorption or tolerance of trial treatment, including difficulty swallowing.≥Grade 2 peripheral neuropathy.Known HIV positive.Participant has current or prior hepatitis B surface antigen positive or hepatitis C antibody positive. Participants must have screening conducted within 14 days before R1.Active systemic infection.Any other medical or psychiatric condition which, in the opinion of the investigator, contraindicates the participant’s participation in this study.Receipt of live vaccination within 30 days prior to R1.


### Interventions and dosing

#### Intervention schedule

The control and experimental interventions for induction (R1) and maintenance (R2) therapy include: lenalidomide, ixazomib, placebo and dexamethasone. At R1, eligible patients will be allocated to one of two interventions with IRD induction; standard up-front dosing followed by toxicity dependent dose modification (reactive), or; frailty score-adjusted up-front dose reductions (adaptive). At R2, eligible patients will be randomised between lenalidomide+ixazomib (R+I) or lenalidomide and placebo maintenance therapy. Table 1 summarises the dosing schedules for R1 and R2. Information regarding dosing due to liver and renal function is provided in online supplemental material.

**Table 1 T1:** Dosing schedule

Randomisation 1			
Treatment	Induction—FIT+induction—standard dosing	Induction—unfit	Induction—frail
Lenalidomide (days=1–21)	25 mg	15 mg	10 mg
Ixazomib (days=1, 8, 15)*	4 mg	4 mg	4 mg
Dexamethasone †(days=1, 8, 15, 22)	40 mg in participants≤75 years 20 mg in participants>75 years	20 mg	10 mg

Randomisation 2		
Treatment	Lenalidomide+placebo maintenance	Lenalidomide+ixazomib maintenance
Lenalidomide (days=1–21)	10 mg†	10 mg†
Ixazomib (days=1, 8, 15)*	N/A	4 mg†
Placebo (days=1, 8, 15)	4 mg†	N/A

*Ixazomib was not used in general multiple myeloma practice at the time of the European Myeloma Network publication. The following licensed dose of Ixazomib will be used for both randomisation arms: 4 mg, at days 1, 8 and 15. This has been studied in patients who are not eligible for transplant and was well tolerated. There have been no studies examining lower doses of Ixazomib so dose reductions are not permitted out of concern for loss of efficacy. The same dose is used irrespective of frailty.

†Or final dose administrated at the end of induction treatment if lower.

As part of their induction therapy, participants in the adaptive arm of R1 will have their dose adjusted according to changes in frailty category at the start of cycles 3, 5 and 7 (For the Myeloma Frailty index, participant’s age is at the time of (Main) Trial registration, therefore, a patient’s frailty will never change based on age only). Doses can also be escalated for suboptimal responders under certain criteria. If after cycle 2, a participant on the unfit or frail dosing strategy has not achieved at least an MR, or required a dose reduction due to toxicity, a request can be made to increase any of their doses to the next highest level at the start of cycle 4. A similar request can be made after cycle 4 for the start of cycle 6, but this requires at least a partial response. These criteria apply for all participants, irrespective of changes in frailty at cycles 3 and 5.

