### Outcomes

#### Primary outcome

For R1, the primary outcome is early treatment cessation (defined as a binary endpoint) for reactive versus adaptive dosing in participants defined to be ‘unfit’ or ‘frail’ at baseline. Participants will be defined to have experienced an event if they die, progress, or are withdrawn from treatment (by the treating clinician) or withdraw consent for treatment, within 60 days of R1.

For R2, the primary outcome is PFS for R+placebo versus R+I, and is defined as the time from R2 to the time of first documented disease progression or death from any cause. Individuals lost to follow-up or progression free at time of analysis will be censored at their last known alive and progression-free date.

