#### Secondary outcomes

The secondary outcomes of this trial are to assess PFS for reactive versus adaptive dosing, time to progression, time to 2nd PFS event, OS, survival after progression, deaths within 12 months of R1, overall response rate, attainment of ≥ very good partial response (VGPR), attainment of minimal residual disease (MRD) negativity (flow MRD will be assessed only. Additional detail on the testing of MRD and timepoints is presented in the ‘central lab analysis’ section of the online supplemental material), duration of response, time to improved response, time to next treatment, treatment compliance and total amount of therapy delivered, toxicity and safety including the incidence of second primary malignancies, quality of life (QoL), cost-effectiveness of reactive versus adaptive dosing of IRD and cost-effectiveness of R+I versus R.

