### Sample size

In total, 740 participants will be enrolled into the trial at R1 to ensure that at least 478 participants remain on trial and are randomised to R2. It is assumed that 65% of those randomised at R1 will be progression free and, therefore, eligible for R2, hence 740 participants are required to be enrolled.

Based on data from the Myeloma XI non-intensive pathway, we hypothesise the frail and unfit patients in R1 will be similar to the older patients in Myeloma XI (>75 years) who have an early treatment cessation rate (within 60 days of R1) of 20%. This hypothesis is based on the expectation that the frailty score is heavily driven by patient age. Younger patients (≤75 years) in the Myeloma XI non-intensive pathway have an early treatment cessation rate of 9%, and it is our hypothesis that our frailty-based dosing schedule has the potential to reduce the rate among the unfit and frail patients to the proportion observed in fit patients.^28 29^

To demonstrate a decrease of 11% in the proportion of early treatment cessation from 20% in the standard dosing schedule arm to 9% in the frailty score-adjusted dose arm among those patients scored at baseline to be unfit or frail would require the recruitment of 324 patients with an allocation ratio of 1:1. These calculations are based on a Pearson’s χ^2^ test without continuity correction, assume a two-sided 5% level of significance, 80% power, and allow for a 1% dropout prior to 60 days post randomisation. Given that we anticipate that 45% of patients will be scored as unfit or frail, by assuming this trial will have a similar underlying population as in Myeloma XI non-intensive pathway and the age distributions in the IMWG report proposing the frailty score,^14^ we would anticipate that we will require 720 patients to enter the trial at R1 to have sufficient unfit and frail patients available to answer this question.

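### The dose-escalation rule for suboptimal responders is misworded: the cycle-6 condition reads backwards, and the cycle-4 toxicity clause can be read as a reason to escalate

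*Protocol article*

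**What the plan says.** The protocol article, Intervention schedule, states the purpose first: "Doses can also be escalated for suboptimal responders under certain criteria".

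Two opportunities follow, both by request:

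- **After cycle 2, for cycle 4.** The request is open if "a participant on the unfit or frail dosing strategy has not achieved at least an MR". A clause joined by *or* then refers to having needed a dose reduction for toxicity.
- **After cycle 4, for cycle 6.** "A similar request can be made after cycle 4 for the start of cycle 6, but this requires at least a partial response".

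The paragraph closes: "These criteria apply for all participants, irrespective of changes in frailty at cycles 3 and 5". That sentence settles how the rule relates to frailty re-scoring. It says nothing about the direction of the response condition.

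Dose modification and discontinuation deals with toxicity. It lets lenalidomide go back up one level on improvement, does not let ixazomib go back up once reduced, and does not restate the escalation rule.

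**The concern.** A rule meant for participants who respond poorly should open when response falls short of a benchmark. The cycle-4 rule does this. The cycle-6 sentence makes reaching PR a condition of the request, so as written the better responders qualify and those below PR do not.

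The toxicity clause in the cycle-4 sentence has a related weakness. It follows a comma and *or*, so it can be taken as a second, free-standing ground for a higher dose: the participant has already needed a reduction for toxicity. In unfit and frail patients that is the less safe of the two readings.

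The wording governs who may be put forward for more drug in the arm whose purpose is to fit dose to frailty. The secondary outcomes it touches include "treatment compliance and total amount of therapy delivered, toxicity and safety", together with the response measures listed in the same section.

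**Working it through.** No figure in the plan depends on this rule, so the check is one of wording and timing.

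**Cycle-6 response condition.** Three readings are possible:

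1. *Literal.* PR or better is needed to make the request. PR, very good partial response and complete response qualify; anything below PR is refused. This contradicts the stated target group.
2. *Literal, with the cycle-4 trigger carried over by the word* similar. The participant must be below MR and at PR or better at the same assessment. Nobody can qualify on response.
3. *Raised benchmark.* The threshold moves from MR to PR, and those who have not reached it may be put forward. This fits the purpose and the cycle-4 rule, but it needs a negation that the sentence lacks.

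Only reading 3 makes sense of the paragraph, and it is not what is written.

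**Cycle-4 toxicity clause.** Two readings are possible:

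1. *One negation covers both parts.* The participant has neither reached MR nor needed a toxicity reduction. Prior toxicity then bars escalation.
2. *Two alternative triggers.* The participant is below MR, or has had a toxicity reduction. Prior toxicity then permits escalation.

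Reading 2 sits badly with Dose modification and discontinuation. For lenalidomide it would largely duplicate the provision for going back up on improvement. For ixazomib it would conflict with the bar on re-escalation, since the request may cover any of the drugs. Reading 1 is the more plausible, but the punctuation leaves reading 2 open.

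**Timing.** With 28-day cycles (Dose modification and discontinuation), counting the first day of cycle 1 as day 1, the earliest start of cycle *k* is day 28 × (*k* − 1) + 1.

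- Cycle 4: 28 × 3 + 1 = day 85.
- Cycle 6: 28 × 5 + 1 = day 141.

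The R1 primary outcome counts death, progression, clinician withdrawal from treatment, or a decision to "withdraw consent for treatment, within 60 days of R1". Both escalation points fall after that window.

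**The pool the rule applies to.** Sample size states that the R1 comparison "would require the recruitment of 324 patients with an allocation ratio of 1:1", and that "we anticipate that 45% of patients will be scored as unfit or frail".

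- 720 × 0.45 = 324, which reproduces the plan's figure.
- 324 / 2 = 162 in the adaptive arm, by baseline category.
- With the planned 9% early cessation: 162 × (1 − 0.09) = 147.4, so about 147 on treatment at day 60, and fewer by cycle 6.

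These figures describe the pool, not the number misdirected. Re-scoring of frailty at cycles 3 and 5 would change the pool. The article gives neither the share reaching PR by cycle 4 nor the expected number of requests, so the number wrongly admitted or refused cannot be derived.

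**Duration.** Cycles 6 to 12 are 7 of the 12 induction cycles. That is a ceiling on what a cycle-6 decision governs, because adaptive-arm doses are also adjusted for frailty at cycle 7.

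**The case against.** The best defence is context. The paragraph limits escalation to suboptimal responders, the second request is called similar to the first, and the PR phrase can be taken as replacing MR as the benchmark. Since one literal reading admits nobody, a clinician is unlikely to apply it. Escalation is by request, which gives a further check. Sites opened under protocol V.2 (Protocol amendments), which is not shown and may be worded correctly.

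Much of this stands. It makes the intent probable and makes harm to participants unproven. It does not make the sentence right: a dosing rule is stated, its plain words point the wrong way, and nothing else in the article restates it.

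A reader might go further and infer that participants are being escalated or refused wrongly. The article does not support this, because it shows neither the V.2 text nor how requests are handled.

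A reader might also see a hard contradiction over ixazomib, since the starred footnote to Table 1 rules out dose reductions while Dose modification and discontinuation, and the dagger on the maintenance dose, assume that they occur. The footnote concerns one starting dose for all frailty groups, and toxicity reductions are handled separately. A qualifier is missing; the rules can be reconciled.

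**Conclusion.** The point holds as an error of wording in a stated dosing rule. The cycle-6 condition is reversed if read literally, and the cycle-4 toxicity clause is ambiguous in a way that matters for safety. It should be corrected, because the rule concerns unfit and frail participants and the correction is almost free.

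Its reach is limited to dose delivered, toxicity and response in the adaptive arm. It would be wrong to infer a threat to the R1 primary result: both escalation points come after day 60, and neither sample size nor alpha depends on the rule. The number affected is unknown.

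The conclusion assumes that the intended benchmark at cycle 6 is failure to reach PR, and that a prior toxicity reduction is meant to rule escalation out at both points. The sponsor's clinicians need to confirm both.

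**What to change.** First compare both sentences with protocol V.2. Then, subject to clinical confirmation, reword along these lines:

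- *After cycle 2, escalation by one dose level from cycle 4 may be requested for a participant on unfit or frail dosing whose response is below MR and who has had no dose reduction for toxicity.*
- *After cycle 4, escalation from cycle 6 may be requested on the same terms with the threshold raised: response below PR, and no dose reduction for toxicity.*

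Optional clarification: in the starred footnote to Table 1, put *frailty-based* before the reference to dose reductions.

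The cost is two sentences and, if wanted, one footnote word, with no change to sample size, alpha or analysis. If V.2 already carries the intended rule, only the article needs a correction. If it does not, the V.3 amendment anticipated in the article is a natural vehicle; the changes listed for it do not mention this rule.
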